## Methods/Design

The MASS-V Trial is an institutional project that the Heart Institute (InCor), Hospital das Clinicas, University of São Paulo designed to prospectively investigate 150 patients with multivessel coronary artery disease (CAD) with normal left ventricle ejection fraction (LVEF) and with a formal indication for CABG or PCI. Fifty patients will be operated on with cardiopulmonary bypass (CPB) and another 50 patients with the same arterial and ventricular conditions and also with a proper indication for myocardial revascularization will be operated on without the help of the CPB circuit. Another 50 patients with CAD and preserved ventricular function with a formal indication for percutaneous coronary intervention (PCI) with the use of intracoronary "stents” will be analyzed.

The inclusion criteria will determine which patients are eligible for which of the three procedures. Anginal symptoms must be stable and the LVEF preserved. The main steps of the procedures are shown in Figure 1. Exclusion criteria include the following: recent myocardial infarction (≤6 months); signs of manifest or suspected infections or rheumatologic disease activity; chronic renal failure (creatinine level >2.0 mg/dL); recent (≤ 6 months) pulmonary embolism or venous thromboembolism; not signing the consent form; contraindication for the use of glycoprotein IIb/IIIa inhibitors or CMR examination, for example, a person with a pacemaker or severe claustrophobia.

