### Biochemistry

Blood samples will be collected from each patient for measurement of troponin I (TnI) and CK-MB mass immediately before PCI and 6, 12, 24, and 36 hours after the procedure. For patients undergoing coronary artery bypass surgery, on-pump or off-pump, these cardiac markers will be measured immediately before surgery and 6, 12, 24, 36, 48, and 72 hours after surgery.

The surgeon and clinical team will be blinded to the CK-MB or TnI data.

All the samples will be centrifuged at 3000 rpm for 20 minutes and analyzed within 2 hours after specimen collection. TnI and CK-MB analysis will be performed in an immunoassay analyzer (ADVIA Centaur, Siemens Health Care Diagnostics, Tarrytown, NY). According to the manufacturer, the lower limit of detection of TnI using a high-sensitivity kit, the Ultra kit, is 0.006 ng/mL, and the 99th percentile and MI reference limits are respectively 0.04 and 0.76 ng/mL. The assay precision, represented by the percentage coefficient of variation (%CV) is ≤ 10 % at 0.03 ng/mL.

The detection limit of the CK-MB mass kit is 0.18 ng/mL, and the cut off values at the 99th percentile, established by our laboratory, are 3.8 ng/mL for women and 4.4 ng/mL for men. The CVs for CK-MB mass, as specified by the manufacturer, are 3.91 % at 3.55 ng/mL and 3.61 % at 80.16 ng/Ml.

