### Statistical analysis

Values will be expressed as mean (±SD) or median (interquartile range) as appropriate. The paired-sample *t* test and the unpaired-sample *t* test will be used to compare means within the study group or between subgroups. *χ*^2^ statistics with Fisher’s exact test will be used for comparison of discrete variables. Continuous variables that were not distributed normally will be compared with the Mann–Whitney *U* test, and correlation between such variables will be made with the Spearman rank test. Binary logistic regression will be performed to determine which clinical and angiographic parameters predict the likelihood of myocardial hyperenhancement. Multivariate logistical regression will be used to assess the relative contribution of various clinical and angiographic variables to the presence of new hyperenhancement after PCI or CABG. A probability value of <0.05 is considered statistically significant.

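### The named tests for continuous data do not fit the design: no paired rank test for skewed before/after data, and only two-sample tests for three groups at an unadjusted 0.05

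*Protocol article*

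**What the plan says.** The protocol article, Statistical analysis, assigns tests to continuous variables as follows.

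- For means, the paired and unpaired *t* tests "will be used to compare means within the study group or between subgroups".
- For skewed variables, "Continuous variables that were not distributed normally will be compared with the Mann–Whitney" U test. This is the only non-parametric comparison test named, and its use is not restricted to independent groups.
- Skewed data are expected: "Values will be expressed as mean (±SD) or median (interquartile range) as appropriate".
- One threshold covers everything: "A probability value of <0.05 is considered statistically significant". No adjustment for several comparisons is mentioned.

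The design produces both paired and three-group data. Methods/Design sets up two surgical groups ("Fifty patients will be operated on with cardiopulmonary bypass (CPB) and another 50 patients with the same arterial and ventricular conditions") and a third group ("Another 50 patients with CAD and preserved ventricular function with a formal indication for percutaneous coronary intervention (PCI"). The text with Figure 1 has every patient scanned before and after the intervention. Under Biochemistry, troponin I and CK-MB are taken "immediately before PCI and 6, 12, 24, and 36 hours after the procedure". Surgical patients have the same times plus 48 and 72 hours.

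**The concern.** A normally distributed before/after variable gets a paired test. A skewed one, read literally, goes to a test that treats a patient's two values as coming from two unrelated patients. Marker levels and the amount of hyperenhanced myocardium are plausible candidates for skewness. If they are analysed this way, the benefit of measuring each patient twice is discarded.

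The second gap is separate. With three treatment groups, someone holding only two-sample tests must compare the groups two at a time. Doing so at 0.05 each raises the chance of declaring a difference between procedures that does not exist.

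The first problem makes real changes easier to miss. The second makes false differences easier to find.

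**Working it through.** The article gives no power, effect size or family-wise error rate to reproduce. The only stated figure is the per-test level of 0.05, taken here as two-sided (sidedness is not stated). Group size is 50 per arm, from Methods/Design. The before/after correlation and the size of the shift are assumptions, because the article gives neither.

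**Skewed pairs.** Let ρ be the correlation between a patient's two values on the log scale. A test for independent samples takes the variance of the difference as proportional to 2σ². The true value is proportional to 2σ²(1 − ρ). For ρ > 0 the test statistic is therefore too small. To a normal approximation, the actual type I error is 2Φ(−1.96/√(1 − ρ)):

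- ρ = 0: 2Φ(−1.96) = 5.0%
- ρ = 0.3: 2Φ(−2.34) = 1.9%
- ρ = 0.5: 2Φ(−2.77) = 0.6%
- ρ = 0.7: 2Φ(−3.58) = 0.03%

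Simulation of 50 log-normal pairs (5,000 runs per setting) agrees on type I error and gives the power for a shift of 0.3 SD on the log scale:

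| ρ | Mann-Whitney type I error | Mann-Whitney power | Signed-rank power, raw values | Signed-rank power, log values |
|---|---|---|---|---|
| 0 | 4.8% | 30% | 28% | 30% |
| 0.3 | 1.9% | 27% | 35% | 40% |
| 0.5 | 0.5% | 23% | 46% | 53% |
| 0.7 | 0.1% | 20% | 67% | 74% |

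Simulation error is at most 1.96 × √(0.25/5,000) = 1.4 percentage points per entry. The signed-rank test kept its type I error between about 4.3% and 5.5% throughout. For a shift of 1 SD or more, with correlation from 0 to 0.7, both tests have power above 99%.

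**Three groups.** Take one continuous variable and three pairwise tests at 0.05. The comparisons share groups, so the large-sample chance of at least one false positive comes from the studentized range with k = 3: P(Q > 1.96 × √2) = P(Q > 2.77) = 12.2%. Simulation with 3 × 50 patients (20,000 runs) gives 12.4% for *t* tests and 12.1% for Mann-Whitney. If the three tests were independent, the figure would be 1 − 0.95³ = 14.3%.

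**After correction.** When no group differs, a Kruskal-Wallis test that must be significant before any pairwise test is read gives 5.0%. Testing each pair at 0.05/3 gives 4.3%. Both figures are per variable. With a separate global test for each of two markers, at an assumed correlation of 0.7 between them, the chance of at least one false positive is about 8% to 9%.

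**The case against.** The strongest reply is that the misuse is inferred. The article never says that before/after pairs will go to Mann-Whitney, and its preceding sentence separates paired from unpaired *t* tests, so the authors know the distinction. That is fair. But if Mann-Whitney is confined to independent groups, skewed pairs have no named test at all, so the sentence needs correcting on either reading. Likewise, pairwise testing of the three procedures is inferred from a reference to subgroups. Yet no named test for a continuous variable accepts three groups. Discrete variables are not affected, since chi-square and Fisher's test handle three groups.

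A second reply is that the main questions hardly use these tests. This stands. The secondary outcomes relate marker levels to fibrosis and ventricular dysfunction. Comparing markers between patients with and without fibrosis is a two-independent-group problem in which Mann-Whitney is valid. Spearman correlation and logistic regression cover other parts, and 5-year death is untouched.

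Two stronger readings are tempting, and the article does not support them.

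- A reader might take the wrong test on pairs to produce false positives. With positive correlation it does the opposite.
- A reader might multiply two markers by four shared sampling times by three pairs, count 24 tests, and quote a far larger family-wise error. The Biochemistry section is a sampling schedule, and nothing in the article plans those 24 comparisons.

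Nor should the widest power gap, at correlation 0.7, be read as the expected loss. The Discussion says that marker release occurs in most patients, so marker shifts may well be large enough for both tests to detect.

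**Conclusion.** The point holds as a defect in how the tests are fixed. It should be corrected, but it does not undermine the trial's main analyses.

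For skewed before/after data, the cost is power only. At a 0.3-SD shift the loss runs from nothing at zero correlation to roughly 47 percentage points (67 − 20) at correlation 0.7, and it disappears for shifts of 1 SD or more. It therefore matters mainly for small changes in highly correlated measures, such as CMR measures that turn out skewed. These sizes rest on log-normal data, 50 pairs, and the assumed correlations and shift.

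For the three procedures, if they are compared pairwise at 0.05, the chance of a false difference is about 12% per continuous variable instead of 5%. This figure needs no assumption beyond equal groups and two-sided tests.

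**What to change.** Revise the Statistical analysis section in about three sentences:

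1. Limit Mann-Whitney to two independent groups, for example fibrosis present versus absent.
2. For skewed within-patient comparisons, use the Wilcoxon signed-rank test, or a paired *t* test on log values.
3. For continuous variables across the three procedures, run ANOVA or Kruskal-Wallis first and read pairwise tests only if it is significant. State that this holds about 5% per variable, and not across both markers.

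If one peak per marker is compared between PCI and CABG, take it over the shared 0 to 36 hour window, because surgical patients are sampled to 72 hours and so have more chances to record a high value.

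The cost is small: no extra patients or measurements, and the Trial status section says that enrolment had not started at submission. The downside is that an isolated pairwise p < 0.05 without a significant global test can no longer be claimed.

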### Trial outcomes

Primary outcome considered is overall death in a 5-year follow-up. Secondary outcomes are levels of CK-MB isoenzyme and I-Troponin in association with presence of myocardial fibrosis and left ventricle ejection dysfunction assessed by CMR.

## Discussion

The release of biomarkers of myocardial necrosis occurs in most patients who undergo mechanical interventions of the heart, both CABG and PCI. Among the causes of this release are the trauma caused by the handling organ, contact of blood with the bypass circuit, aortic cross clamping, and reperfusion injury. On the other hand, periprocedural myocardial injury during PCI can result from procedural complications, such as distal embolization, side-branch occlusion, coronary dissection, and disruption of collateral flow.

The clinical significance and long-term prognosis of this condition continues to be debated. Initial short-term follow-up found no increase in the incidence of cardiac events; however, further large prospective trials have suggested that elevation of biomarkers of myocardial necrosis after PCI or CABG is clinically relevant. In addition, outcomes after CABG or PCI with very high procedural TnI or CK-MB levels have prognostic implications considered similar to those of spontaneous acute myocardial infarction.

Delayed enhancement CMR imaging can quantify irreversible myocyte necrosis for the identification of subedocardial infarction.

However, uncertainties remain about the mechanisms and functional significance of the release of cardiac biomarkers and the direct relationship between procedure-related troponin and CK-MB increase and the degree of myocardial tissue loss.

### Ethical considerations

MASS-V trial will be conducted in accordance with the principles of the Declaration of Helsinki and with laws and regulations of our country. The Ethics Committee of the Heart Institute of the University of São Paulo, Brazil, approved the study protocol. The attending physician will obtain written informed consent from the all study participants.

### Trial status

This is a proposed trial and the enrollment process has not started until the date of manuscript submission.

## Abbreviations

AMI: Acute Myocardial Infarction; CABG: Coronary Artery Bypass Graft; CMR: Cardiac Magnetic Resonance; CPB: Cardiopulmonary Bypass; CPK: Creatine Phosphokinase Enzymes; CK- MB: Creatine Kinase Isoenzyme; CAD: Coronary Artery Disease; CPB: Cardiopulmonary Bypass; CV: Coefficient of Variation; DE-CMR: Delayed Enhancement CMR imaging; LVEF: Left Ventricle Ejection Fraction; MASS: Medicine, Angioplasty, or Surgery Study; PCI: Percutaneous Coronary Intervention; SD: Standard Deviation; TnI: Troponin I.

